## Abstract

**Background:**

Intermittent preventive treatment in pregnancy (IPTp) with sulfadoxine-pyrimethamine (SP) is an important malaria control strategy in sub-Saharan Africa. Indeed, it overcomes the risk of misdiagnosis due to low peripheral parasitemia during pregnancy by treating women with SP on predetermined schedules. However, over time, the spread of *Plasmodium*-resistant strains has threatened this strategy in many countries. As an alternative, the intermittent screening and treatment for pregnancy (ISTp) aims at a monthly screening of pregnant women, preferably by using very sensitive tests such as ultrasensitive rapid diagnostic tests (us-RDTs) and the treatment of positive cases with artemisinin-based combination therapy (ACT) regardless of the presence of symptoms. Unlike IPTp-SP, ISTp prevents overuse of antimalarials limiting the drug pressure on parasites, an advantage which can be potentiated by using an ACT like pyronaridine-artesunate (Pyramax®) that is not yet used in pregnant women in the field.

**Methods:**

This study aims to compare the non-inferiority of ISTp using us-RDTs and Pyramax® versus IPTp-SP on malaria in pregnancy through a randomized clinical trial performed in Kisenso, Kinshasa, the Democratic Republic of the Congo, a malaria perennial transmission area.

**Discussion:**

The results will be essential for the National Malaria Control Program to update the malaria prevention policy in pregnant women in the Democratic Republic of the Congo.

**Trial registration:**

ClinicalTrials.gov NCT04783051

## Administrative information

Note: the numbers in curly brackets in this protocol refer to SPIRIT checklist item numbers. The order of the items has been modified to group similar items (see http://www.equator-network.org/reporting-guidelines/spirit-2013-statement-defining-standard-protocol-items-for-clinical-trials/).

## Introduction

### Background and rationale {6a}

Malaria is a significant health threat for pregnant women and their offspring in endemic settings [1, 2]. Indeed, *Plasmodium falciparum* (*Pf*) can be sequestered in the placenta during pregnancy, resulting in low peripheral parasitemia. As a consequence, standard malaria diagnostic tests can be false negative in pregnant women who actually do have a *Pf* malaria infection [3, 4].

Intermittent preventive treatment of pregnant women (IPTp) with sulfadoxine-pyrimethamine (SP) is one of the World Health Organization (WHO)’s recommended malaria prevention strategies in pregnant women in sub-Saharan African countries [2]. The IPTp-SP strategy overcomes the potential misdiagnosis of malaria in pregnant women by treating them systematically with at least three doses of SP during antenatal care (ANC) visits [5]. It can be administered from the beginning of the second trimester until delivery, provided that doses are given 1 month apart. However, in many countries, the spread of *P. falciparum* SP-resistant strains now threatens the efficacy of the IPTp-SP and can lead to the proliferation of placental-resistant parasites in pregnant women [6–10].

As an alternative for IPTp-SP, intermittent screening and treatment for pregnancy (ISTp) is considered as an option [11]. The latter entails monthly screening of pregnant women with a malaria rapid diagnostic test (RDT) and treatment of positive cases with an artemisinin-based combination therapy (ACT) regardless of the presence of symptoms. The ISTp relies on the performance of the diagnostic tests and this strategy is currently jeopardized due to false negative *P. falciparum* histidine-rich *Pf*HRP2-based RDT, the most commonly used diagnostic test to support this approach [12, 13]. The *Pf*HRP2-based RDTs have been found to detect around 45% of the PCR-positive infections in paucigravidae and about 30% in multigravidae, thereby allowing the majority of infections to persist in the placenta [14]. To circumvent this limitation, the use of ultra-sensitive RDTs (us-RDTs), which have a higher sensitivity than conventional RDTs [11, 14], is proposed as an alternative as these can avoid false negative test results [15].

Unlike IPTp-SP, ISTp limits the overuse of antimalarials and, thus, reduces drug pressure on malaria parasites [11]. This advantage could be potentiated by using an ACT that is currently not yet broadly used or should not be used by the national malaria control program for treating other strata of the population than pregnant women. Pyronaridine-artesunate (Pyramax®), a newly approved antimalarial drug is the ideal candidate for this purpose. Indeed, Pyramax®, approved for use in malaria-endemic countries since 2015, is now used in the field to treat malaria in children and adults [16].

This study hypothesized that the ISTp performed with the us-RDT and, if positive, followed by Pyramax® treatment (ISTp-US-Py) is non-inferior to IPTp-SP for the prevention of maternal malaria, maternal anemia, spontaneous abortions or intrauterine death during pregnancy, fetal morbidity (premature birth, low birth weight, small for gestational age), and neonatal mortality at childbirth.

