### Secondary objectives

The secondary objectives are to assess that:

During pregnancy:The proportion of asymptomatic/symptomatic malaria cases is not higher when using ISTp-US-Py compared to IPTp-SPThe proportion of the parasite densities is not higher when using ISTp-US-Py compared to IPTp-SPThe proportion of anemia is not higher when using ISTp-US-Py compared to IPTp-SPThe incidence of spontaneous abortions or intrauterine deaths is not higher when using ISTp-US-Py compared to IPTp-SP

At birth:

In women:The proportion of asymptomatic/symptomatic malaria cases is not higher when using ISTp-US-Py compared to IPTp-SPThe parasite densities are not higher when using ISTp-US-Py compared to IPTp-SPThe proportion of anemia is not higher when using ISTp-US-Py compared to IPTp-SP

In the offspring including:Intrauterine deathThe fetal morbidities (preterm birth, low birth weight) are not higher when using ISTp-US-Py compared to IPTp-SP

During the 28-day period following the birth:The neonatal and early neonatal mortality of the offspring is not higher when using ISTp-US-Py compared to IPTp-SP

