### Sample size {14}

The calculation of the sample size has performed using the Sealed Envelope Ltd. 2012. Power calculator for binary outcome non-inferiority trial. [Online] Available from: https://www.sealedenvelope.com/power/binary-noninferior/.

Referring to the results of a study comparing IPTp-SP and IST (dihydroartemisinin-piperaquine) [11], the number of participants required to detect a difference of 10% with a significance level of 5% and a power of 80% to assess the non-inferiority of IST to IPTp-SP vary as described in Table 2. Variables of interest considered were the malaria status, the anemia status, and the low birth weight rate.

**Table 2 Tab2:** Variation of the sample size according to the difference of the outcome of interest

	IPTp	IST	Sample size
Low birth weight	10.5	15.7	122
Malaria infection	18.9	23.4	196
Anemia	30	25	220

*NB*: IST with dihydroartemisinin-piperaquine and standard RDT was used as an example to calculate the sample size for the current study as there are no previous studies could be found that include assessment of Pyramax® and us-RDT for use as IST.

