## Statistical methods

### Statistical methods for primary and secondary outcomes {20a}

#### General analysis principles

Data analysis will be performed after the end of the follow-up period of the last participant included in the study.

Study participants will receive two different interventions depending on which group they are enrolled in. The first group will undergo intermittent screening during pregnancy using ultra-sensitive malaria rapid diagnostic test and treatment with pyronaridine-artesunate—Pyramax® (ISTp-US-Py), and the second group will receive an intermittent preventive treatment as suggested by the NMCP. The analysis will mainly compare the two groups to assess the outcomes of the study. All AEs (severe or non-severe) will be reported in the trial publication and compared in the study arms and gestational weeks. To assess the effect of the study interventions in the IPT and the ISTp arms, we will use the intention-to-treat approach. Meaning that all the participant who has been randomized to an arm or another will be considered as part of that arm for the analysis despite their level of completion.

Data from every woman included with baseline and at least one further visit will be analyzed in the treatment arms to which they were assigned. Safety data from all participants who received at least one dose of the study drug will be used in the analysis to describe AEs. AEs will be grouped by treatment group for the number of events and number of participants with type of event. Descriptive statistics will be summarized by treatment arm and visits.

For all statistics, the confidence intervals will be two-sided and at the 95% level, and the value of *p* < 0.05 will be interpreted as statistically significant.

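### The non-inferiority hypothesis covers fetal loss and neonatal death, but the only stated margin (10 points) is tied to other outcomes and about 220 women cannot support a claim on deaths

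*Protocol article*

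**What the plan says.** The hypothesis closing Background and rationale {6a} is that the screening strategy "is non-inferior to IPTp-SP for the prevention of maternal malaria, maternal anemia, spontaneous abortions or intrauterine death during pregnancy". The list continues through fetal morbidity "and neonatal mortality at childbirth". Explanation for the choice of comparators repeats this list as what non-inferiority will be assessed for. The Main objective extends non-inferiority to the impact of maternal malaria and anemia on the offspring.

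Under Secondary objectives the death outcomes are worded as not higher. For the 28 days after birth, the aim is to show that the "neonatal and early neonatal mortality of the offspring is not higher when using ISTp-US-Py compared to IPTp-SP". Spontaneous abortion and intrauterine death have the same form.

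Only Sample size {14} gives a difference: "the number of participants required to detect a difference of 10% with a significance level of 5% and a power of 80" per cent. The next sentence says what it is for: "Variables of interest considered were the malaria status, the anemia status, and the low birth weight rate". No death outcome appears there or in Table 2, and no fetal-loss or neonatal-death rate is given anywhere. Recruitment {15} takes 220 women as the minimum and 242 (121 per arm) after allowance for losses. General analysis principles states that "the confidence intervals will be two-sided and at the 95% level".

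**The concern.** A non-inferiority claim needs a margin that would matter clinically for that outcome, and enough information to exclude it. For fetal loss and neonatal death the protocol makes the claim and supplies neither. Ten points is a wide margin for an outcome that may occur in only a few per cent of women: whenever the control risk is below 10%, a doubled risk lies inside it.

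The protocol intends the results to inform the national malaria programme's prevention policy. A statement that the new strategy is non-inferior for deaths would carry weight there, and the design could not support it.

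**Working it through.** **1. What the 10% means.** Sizing formula: n per arm = (z₁₋α + z₀.₈₀)² × [p₁(1−p₁) + p₂(1−p₂)] / (0.10 + d)², where d is the assumed difference counted in favour of screening. With one-sided α = 0.05, the squared z-sum is (1.645 + 0.842)² ≈ 6.183.

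- Anemia (30 v 25): 6.183 × 0.3975 / 0.15² = 109.2, so 110 per arm and 220 in total.
- Malaria (18.9 v 23.4): 6.183 × 0.332523 / 0.145² = 97.8, so 98 per arm and 196 in total.
- Low birth weight (10.5 v 15.7): 6.183 × 0.226326 / 0.152² = 60.6, so 61 per arm and 122 in total.

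All three totals match Table 2. The 10% is therefore an absolute margin of 10 points, and the minimum of 220 is 110 per arm. (Reproducing the malaria and low birth weight rows requires counting the higher rate under screening as favourable. That is a separate matter and does not affect what follows.)

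**2. What the 10 points would do for deaths, if used.** Inputs: 110 per arm; non-inferiority declared when the upper limit of the two-sided 95% interval for the risk difference (screening minus IPTp-SP) is below 0.10; true risk doubled from p to 2p. The control risks p are assumptions.

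Normal approximation: probability = Φ{(0.10 − p)/SE − 1.96}, with SE = √{[p(1−p) + 2p(1−2p)]/110}. At p = 2%, SE = √(0.0580/110) = 0.02296, and (0.08/0.02296) − 1.96 = 1.52, so the probability is 94%.

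With so few events the approximation is rough. The last two columns therefore sum exact binomial probabilities over all pairs of event counts for which the interval passes.

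| Control risk to doubled risk | Normal approx. | Exact, Newcombe | Exact, Wald |
|---|---|---|---|
| 1% to 2% | >99% | 97% | 99% |
| 2% to 4% | 94% | 80% | 91% |
| 3% to 6% | 71% | 58% | 70% |
| 4% to 8% | 47% | 40% | 48% |
| 5% to 10% | 29% | 27% | 31% |

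The probability falls to one half at a control risk of about 3.4% (Newcombe) or 3.9% (normal approximation). With 121 per arm the probabilities are slightly higher, for example 86–94% for 2% to 4%.

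**3. Whether a tighter margin could rescue the claim.** To exclude a doubling (margin equal to p) with equal true risks, 80% power and one-sided 2.5%: n per arm = 7.849 × 2p(1−p)/p² = 15.70 × (1−p)/p.

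- p = 1%: 1,555 per arm, 3,110 in total.
- p = 2%: 770 per arm, 1,540 in total.
- p = 3%: 508 per arm, 1,016 in total.

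The trial plans 242.

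**The case against.** The strongest reply is that the test in step 2 is not in the protocol. Sample size {14} names the three outcomes the 10% serves, the death outcomes are secondary, and the analysis is to follow a separate plan that is not at hand and may set other margins or none. This stands in part: applying 10 points to deaths is an inference from the absence of any other figure, and the table must be read as conditional on it. It does not remove the point. The hypothesis and objectives claim non-inferiority for deaths in the protocol itself, and step 3 shows that a separate margin cannot supply the missing information.

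A second reply is that the result depends on assumed risks. That also stands. At 4–5% a doubling no longer usually passes, although 27–31% at 5% is still far above the nominal 2.5%. A reader might infer that 10 points dwarfs any plausible death rate; the documents give no rate on which to base that.

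Two other stronger readings should be avoided:

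- A reader might say that the margin accepts low birth weight rising from 10.5% to 20.5%. It does not. The margin is the value to be excluded, and with those true rates and 110 per arm non-inferiority would be declared only 2.5% (Newcombe) to 2.8% (Wald) of the time.
- A reader might infer that a non-significant p-value will be read as showing that deaths are not higher. General analysis principles says only what counts as significant. It does not say how non-significance will be read.

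**Conclusion.** The scope of the non-inferiority hypothesis is too broad. It includes fetal loss and neonatal death, for which the protocol gives no margin and no sizing, in a trial of 220–242 women. If the only stated margin were applied, a doubling of risk would pass more often than not at control risks up to about 3.4–3.9%, and in roughly a quarter to a half of trials at 4–5%. These figures rest on 110 per arm, a two-sided 95% interval, assumed control risks of 1–5%, and the inference that 10 points would be used.

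The conclusion that the trial cannot support a non-inferiority claim on deaths does not depend on that last inference: excluding a doubling at 1–3% needs about 1,000 to 3,100 women. The malaria comparison, which is the primary outcome, is not affected by this point.

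**What to change.** In Background and rationale {6a}, Main objective and Explanation for the choice of comparators, limit the non-inferiority hypothesis to the outcomes for which Sample size {14} states the 10-point margin: malaria, anemia and low birth weight. In Secondary objectives, reword fetal loss and neonatal death as estimation: risk differences and risk ratios with 95% intervals. State that neither a non-significant difference nor an interval lying inside 10 points will be taken as evidence that deaths are not higher.

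This is a change of wording. Recruitment is complete, so more women are not an option, but the analysis follows the last participant's follow-up, so at the time of writing the change could still be made before it. The cost is that the trial can claim less about the offspring.

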### Objectives {7}

#### Main objective

The main objective of the study is to assess that the proportion of maternal malaria, maternal anemia, and their impact on the offspring is non-inferior when using ISTp-US-Py compared to IPTp-SP.

### Secondary objectives

The secondary objectives are to assess that:

During pregnancy:The proportion of asymptomatic/symptomatic malaria cases is not higher when using ISTp-US-Py compared to IPTp-SPThe proportion of the parasite densities is not higher when using ISTp-US-Py compared to IPTp-SPThe proportion of anemia is not higher when using ISTp-US-Py compared to IPTp-SPThe incidence of spontaneous abortions or intrauterine deaths is not higher when using ISTp-US-Py compared to IPTp-SP

At birth:

In women:The proportion of asymptomatic/symptomatic malaria cases is not higher when using ISTp-US-Py compared to IPTp-SPThe parasite densities are not higher when using ISTp-US-Py compared to IPTp-SPThe proportion of anemia is not higher when using ISTp-US-Py compared to IPTp-SP

In the offspring including:Intrauterine deathThe fetal morbidities (preterm birth, low birth weight) are not higher when using ISTp-US-Py compared to IPTp-SP

During the 28-day period following the birth:The neonatal and early neonatal mortality of the offspring is not higher when using ISTp-US-Py compared to IPTp-SP

### Trial design {8}

This is a 2-arm randomized (1:1 ratio) non-inferiority trial. A unique registration number will be associated with a randomization list number, generated before the start of the study and which will determine the assignment of study participants to one of the study arms.

## Methods: participants, interventions, and outcomes

### Study setting {9}

The study is carried out in DRC where malaria transmission is intense and perennial.

The study is conducted in the “Maternité Esengo,” a 106-bed health facility, located in Kisenso, Kinshasa, where there is an average of 100 deliveries per month. A previous study performed in a similar setting showed that the prevalence of malaria in pregnant women was 30% [4].

Pregnant women will be recruited during ANC visits, regardless of their parity.

### Eligibility criteria {10}

Inclusion criteria (all should be present):Gestation ≥16 weeksAge: ≥18 yearsResidence within the health facility catchment areaWillingness to adhere to study requirements and to deliver at the health facilityWillingness to provide written informed consent; if the woman is illiterate, she can choose an impartial witness, not related to the study, to accompany her during the consent process and they will both sign the informed consent form

Exclusion criteria:Known history of allergy to SP or to an ACTAn ongoing antibiotic prophylaxis with cotrimoxazoleCurrent issue requiring hospital admission (including severe malaria as defined by WHO) [17]Pregnancy at high riskWomen before 16 weeks of pregnancy will not be included because there is insufficient data on the safety of Pyramax® during the first trimester of pregnancy. However, if the WHO changes the recommendations, women in the first trimester could be treated with ACT. In this case, a modification of this protocol will be done accordingly and subjected to ethical review and to competent authorities

Participants will be excluded in case of withdrawal of the informed consent, if they take antimalarial or an antibiotic with antimalarial activity other than those prescribed by the study clinician.

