#### Criteria for discontinuing or modifying allocated interventions {11b}

Changing the distribution of intervention is not possible in the framework of this study. In the event of an allergy or other adverse event (AE) that may impact participants’ health or that of the offspring, the participant will be removed from the study and will no longer receive the intended drug in the arm in which they were allocated.

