#### Procedure for unblinding if needed {17b}

Not applicable. The study team and the participants themselves will all be aware of the arms where participants will be included.

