### Plans to promote participant retention and complete follow-up {18b}

Participant’s visits are scheduled on monthly basis. In case of a missing visit, the site clinicians will be in charge to phone the participants to enquire for the reason of the missing visit and encourage them to come to the study site. In case participants cannot be reached by phone, a community health worker will be visiting the households for enquiring and encourage participants to come to the study site. In case participants are not reachable, they will be considered as lost to follow-up after 3 missing visits and all attempts to reach out to them will be documented.

In case of loss to follow-up, all the data collected during the woman participation in the study will be used for the analysis. However, in case of consent withdrawal, the participant data will not be used for the analysis.

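### Removal rules after randomisation contradict the stated intention-to-treat analysis; the rule on outside antimalarials may lose malaria cases selectively, with a bias whose direction depends on the arm

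*Protocol article*

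**What the plan says.** All references are to the protocol article.

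- **Trial design {8}:** "This is a 2-arm randomized (1:1 ratio) non-inferiority trial".
- **General analysis principles (under {20a}):** the efficacy approach is ITT, explained as "all the participant who has been randomized to an arm or another will be considered as part of that arm for the analysis", however much of the trial each woman completes. The next paragraph narrows this: "Data from every woman included with baseline and at least one further visit will be analyzed".
- **Eligibility criteria {10}:** after the entry criteria, participants are to be excluded if they withdraw consent, or "if they take antimalarial or an antibiotic with antimalarial activity other than those prescribed by the study clinician". The reference to the study clinician's prescriptions shows that the rule operates after enrolment.
- **Criteria for discontinuing or modifying allocated interventions {11b}:** after an allergy or another adverse event that may affect mother or offspring, "the participant will be removed from the study". Stopping the drug is mentioned as well, so removal is more than stopping treatment.
- **Plans to promote participant retention {18b}:** "in case of consent withdrawal, the participant data will not be used for the analysis". Data from women lost to follow-up are kept.
- **Section {20c}:** each variable is tested on whatever data are available.
- **Procedure for unblinding {17b}:** "The study team and the participants themselves will all be aware of the arms where participants will be included".

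**The concern.** A plan cannot both count every randomised woman and exclude some of them after randomisation. As written, a data manager would not know whether a woman who took an outside antimalarial is in or out of the ITT set, or whether her delivery and day-28 outcomes are to be collected.

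The outside-antimalarial rule matters most because it is close to the primary outcome, malaria status at each visit. A woman who obtains an antimalarial elsewhere may well have done so because she had, or was thought to have, malaria. Removing her can remove a case. In a superiority trial an equal loss of cases from both arms is usually conservative. In a non-inferiority trial it shrinks an unfavourable difference and makes the claim easier.

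The arms could also differ in how often this happens. Women and staff know the allocation, and a woman in the ISTp arm with a negative test receives no study antimalarial at that visit, whereas the IPTp arm receives SP on a schedule. The adverse-event rule raises the same problem for pregnancy and neonatal outcomes, because a woman taken out of the study before delivery may contribute none.

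**Working it through.** **Step 1. The statements side by side.**

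| Event after randomisation | ITT definition | Other rule |
|---|---|---|
| Outside antimalarial | analysed in her arm | excluded ({10}) |
| Allergy or certain adverse events | analysed in her arm | removed from the study ({11b}) |
| Consent withdrawal | analysed in her arm | excluded ({10}); all data discarded ({18b}) |
| No visit after baseline | analysed in her arm | not analysed ({20a}, next paragraph) |
| Loss to follow-up | analysed in her arm | data so far are used ({18b}): consistent |

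Only the last row agrees.

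**Step 2. The plan's own sample size.** The total rests on the anemia row of Table 2 (30% versus 25%, margin 10 points, 80% power). At one-sided 5%, with z-values 1.645 and 0.842:

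n per arm = (1.645 + 0.842)² × (0.30×0.70 + 0.25×0.75) / (0.10 + 0.05)² = 109.2, rounded up to 110, or 220 in total. Then 220 × 1.10 = 242, or 121 per arm. This reproduces.

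**Step 3. Effect of losing cases.** Inputs:

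- control malaria risk 18.9% (Table 2);
- ISTp risk 28.9%, which is 18.9% plus the 10-point margin, so ISTp is truly at the limit;
- 121 per arm ({15});
- two-sided 95% intervals ({20a}), which is one-sided 2.5% for non-inferiority;
- share f of malaria cases lost: **an assumption**, since the protocol gives no figure.

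Observed risk in an arm with true risk p: q = p(1 − f)/(1 − pf). Women remaining: 121(1 − pf).

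With f = 0.20:

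- ISTp: q = 0.289 × 0.8 / (1 − 0.0578) = 0.245, with 114.0 women left. About 7 of 35 expected cases are lost.
- IPTp: q = 0.189 × 0.8 / (1 − 0.0378) = 0.157, with 116.4 women left.

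Probability of declaring non-inferiority = Φ[(0.10 − d)/SE − 1.96], where d is the observed excess and SE² = q₁(1 − q₁)/n₁ + q₂(1 − q₂)/n₂.

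Example, loss in ISTp only: d = 0.0564, SE = 0.0538, (0.10 − 0.0564)/0.0538 = 0.81, and Φ(0.81 − 1.96) = Φ(−1.15) = 12.5%.

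| Cases lost (assumed) | Observed excess, points | False non-inferiority, one-sided 2.5% |
|---|---|---|
| none | 10.0 | 2.5% |
| 10% of all women, unrelated to outcome, both arms | 10.0 | 2.5% |
| 10% of cases, both arms | 9.4 | 3.2% |
| 20% of cases, both arms | 8.8 | 4.1% |
| 30% of cases, both arms | 8.1 | 5.6% |
| 20% of cases, ISTp only | 5.6 | 12.5% |
| 20% of cases, IPTp only | 13.2 | 0.5% |

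At one-sided 5%, the level at which the sample size reproduces, the three 20% rows become 7.8%, 20.2% and 1.2%, against 5%.

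The model treats a lost case as contributing nothing. If a positive test before removal still counts, the effect is smaller.

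**The case against.** Several points on the other side have force.

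- **What is deleted.** Only consent withdrawal explicitly discards data already collected. For outside antimalarials and adverse events the text speaks of exclusion or removal and does not say that earlier results are dropped. Malaria is assessed at every visit, so earlier positives may still count. This stands, and it limits the clear risk to outcomes after removal.
- **How many women.** Section {11d} advises unwell women to return to the health center, and antimalarials prescribed by the study clinician do not trigger the rule. It affects only women treated elsewhere, and no frequency is given. This stands.
- **Direction.** A reader might infer that the rules always make non-inferiority easier to show. The documents do not support that. Equal loss of cases, or more loss in the ISTp arm, has that effect; loss mainly in the IPTp arm does the opposite; loss unrelated to outcome leaves the error rate unchanged. Nothing in the protocol says which arm would lose more.
- **Only one analysis set.** A reader might also infer that a per-protocol analysis has been ruled out. Section {20b} is about subgroups, and the data management section refers to a separate analysis plan, which is not shown and may define further sets. Its absence from the article is not an error.
- **Convention.** Requiring one visit after baseline is a common modified ITT for an outcome measured at visits, and discarding data after consent withdrawal is a disclosed choice. Both are defensible in themselves, but neither matches the definition of ITT given.

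None of this reconciles the rules with the ITT statement. An unseen analysis plan cannot do so fully either: if women are not followed after removal, their later outcomes do not exist to be analysed.

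**Conclusion.** The contradiction is firm and follows from the text alone: the protocol promises an analysis of all randomised women and elsewhere removes some of them, in one case for a reason plausibly linked to the primary outcome.

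The bias is a possibility, not a demonstrated effect. On an assumed loss of 20% of cases at a true 10-point excess, the chance of a false non-inferiority claim would be about 4.1% (both arms), 12.5% (ISTp only) or 0.5% (IPTp only), against a nominal 2.5%. These figures depend on the assumed share, on the loss being tied to malaria, and on removed cases contributing nothing. The 12.5% figure is the adverse end of that range and should not be read as an expectation.

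**What to change.** Reconcile Eligibility criteria {10}, section {11b} and section {18b} with the ITT statement in {20a}, on data use and follow-up only. Whatever is decided about study drug is a separate clinical matter. The text should state that:

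1. taking a non-study antimalarial, or having an allergy or adverse event, does not end follow-up and does not remove a woman from the ITT set;
2. every woman is followed to delivery and day 28 unless she withdraws consent;
3. data collected before withdrawal are kept where consent allows;
4. any restriction to women with a visit after baseline is named as a modified ITT set, with the number omitted given by arm;
5. non-study antimalarials, already recorded at visits, are reported by arm.

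Add one sensitivity analysis that counts outside treatment for suspected malaria as a malaria event. Keep the us-RDT definition as primary, since such treatment is often unconfirmed. A supportive per-protocol analysis is advisable if the analysis plan does not already contain one.

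Cost: a short amendment, continued follow-up of women who already have scheduled visits, and one extra analysis. Trial status says that recruitment is complete but the last visit is still to come, so part of this can still be done. Women already removed may not be recoverable; their number, reason and timing should be reported by arm.
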